**Knowledge transfer**

KT was defined by a consensus of experts by the World Health Organization (WHO) in 2005, as "the synthesis, exchange and application of knowledge by decision makers to accelerate the benefits of local and global innovation, strengthening health systems and improving the health of people”. The successful transfer of knowledge was conceptualized as a supply or dependent factor (availability of evidence, appropriate packaging, evidence-based messages) and demand or demand factors (local knowledge, political support for the implementation of scientific research, strategic presence of decision makers) [14]. KT barriers are also divided into demand factors such as poor access to relevant tests, production costs, packaging and distribution of technologies necessary for KT [10].

Doctors rarely follow evidence-based guidelines [14, 21]. Likewise, managers and policy makers ignore solid evidence when designing services or allocating resources [10]. Solutions to these problems involve the controlled supply of research evidence or the formation of demand for evidence through education, facilitation, financial incentives or the use of technology adoption channels. KT tries to overcome this challenge through strategies based on three assumptions. The first of these is that "knowledge" is provided by the results of objective and impersonal investigations; that is, it is provided by explicit, consistent and reproducible knowledge. Normally this is shown in the results of randomized clinical trials or meta-analysis and in all cases the knowledge is seen as information that the professionals who generate it can use. The second assumption is that it is useful in KT to conceptualize the "know-how" gap between scientific facts and practice; this implies that knowledge and practice can be separated both empirically and analytically. The third assumption is that the practice consists of a series of rational decisions, in which the results of scientific research can be used as support [10, 12].

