Neuromarketing is an interdisciplinary field that seeks to evaluate, through neuroscientific methods, the cognitive and emotional responses of consumers to various marketing stimuli, uniting neuroscience, psychology and marketing [32]. Several indicators are measured and evaluated under this strategy, and include emotional commitment, memory and recall, knowledge, attention, and intention to buy. Therefore, the clear formulation and adequate understanding of the message received, as well as the activation of attention and emotion mechanisms, will be able to predict the retention capacity and to a certain extent the effectiveness of the commercial or campaign [22].

Neuromarketing uses different methods that allow the recording of brain electrical activity and metabolic activity. One of the most widely used methods is electroencephalography (EEG), a non-invasive method that detects electrical signals produced by brain activity through sensors. Using the concept that different brain areas are responsible for different functions, depending on the type of stimulus specific cortical areas will be activated [33]. Other techniques that record brain electrical activity, such as functional Magnetic Resonance Imaging (fMRI) and Positron Emission Tomography (PET), are costly methods that limit their application in some way [22].

Another method widely used in neuromarketing makes use of the measurement of ocular dynamics by means of the eye-tracking technique, used to detect and record the activity of eye movements, and establishing during the assignment of a visual task a measurement of the relationship between these movements and cognitive processes such as the processing of language and images, memory processes, social cognition and decision making [34]. The autonomous response of an individual produced by a stimulus is also used in this discipline through the measurement of changes in heart rate and electrodermal reactivity through the galvanic response of the skin, which is related to changes in the sympathetic system associated with emotion, cognition and attention [33, 35].

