The mechanisms of the programs are described as underlying processes, which refers to how interventions modify the outcomes and explain the impact of the program on each individual from the source of the intervention [10]. Regarding the measurement of outcomes, programs or interventions should be tested against a range of indicators for each of the outcomes, both for measurements before and after applying these interventions [9, 19].

Currently there is no measurement representing potential changes in the outcomes of KT in the field of maternal and neonatal health, so it is therefore necessary to look for tools to measure changes at the level of knowledge, understanding or attitudes. Additionally, these should be reasonably associated with potential causal mechanisms within interventions focused on the KT [46].

KT strategies are divided into those that "push" or "pull" knowledge. The strategies that "push" take into account efforts that increase the flow of knowledge between those entities or people that generate knowledge and those who can benefit from it. This involves a process of synthesis of information, as well as efforts for the distribution and promotion of this information. In health care, this type of strategy may involve scientific publications, reports, systematic reviews, clinical practice guidelines, online material, courses, and presentation at conferences, among others.

On the other hand, KT strategies that "pull" knowledge are those in which people seek to obtain new knowledge, in such a way that the entities that provide health care, policy makers or patients actively seek the knowledge they need to make decisions. These efforts can be facilitated with an effective search tool to locate the necessary information, as well as training in the identification and application of research results.

This can be successfully applied with three groups of key decision makers:

1. Allied health care providers and professionals.
2. Patients and the general public.
3. Decision makers.

The structure of the KT developed by Graham *et al*. focuses mainly on the support and promotion of the implementation of scientific evidence, while Kitson *et al*. proposes that there are several types of knowledge that are necessary to develop an effective KT intervention: investigation of evidence, knowledge of the subject and the local context, as well as the experience of the participants [40].

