1. **Specific objectives**

- Determine the effectiveness of different strategies of social appropriation of knowledge through a systematic review of the literature.
- Based on scientific evidence and expert opinion, design 12 capsules of knowledge in maternal and neonatal health.
- Evaluate the effectiveness of the capsules in maternal and neonatal health in terms of social appropriation of knowledge, measured from attention, emotional response and recall through a pilot study, applying neuromarketing strategies.
- Produce a final version of the knowledge capsules in maternal and neonatal health with the design and content defined in the previous phases.

1. **Methodology**

The development of the project will be developed in 6 phases:

1. Systematic review of the literature.
2. Preliminary definition of the contents of the knowledge capsules in maternal and neonatal health.
3. Formal consensus of experts under the modified Delphi method where the content and strategies to be used in them will be defined.
4. Design and development of health capsules in maternal and neonatal safety.
5. Evaluation of the effectiveness of the knowledge capsules in maternal and neonatal health through a neuromarketing strategy, with a crossover experimental study.
6. Final production of health knowledge capsules in maternal and neonatal safety
7. **Phase 1. Systematic review of the literature and meta-analysis**

***- Design of the study:*** A Systematic Review of Literature (RSL) will be carried out, with the objective of reviewing and critically evaluating the literature on the effectiveness of different strategies in the transfer and social appropriation of knowledge in health. This RSL will include randomized clinical trials. In the event that this level of evidence is not found, we will proceed to look for cohort studies that evaluate this type of interventions in the general population.

***- Research question:*** the orientation of all steps in the development of the RSL, are within the framework of the following question:

In pregnant women, what is the effectiveness of KT strategies in health that include audiovisual methods, compared with other similar strategies (written material, talks with health personnel, etc.)?

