During the screening of the health knowledge capsules, the eye tracking method will be applied to evaluate the attention of the subjects before the visual stimulus of the health capsules. By means of a Tobii TX 300 eye tracker and the Tobii Studio Software, the pupillary size in arbitrary units (AU), and the duration and direction of the fixation in seconds will be measured. Areas of interest will also be recorded, according to the stimuli in which the attention is fixed, the duration, and the order in which the visual exploration is performed.

The monitoring of the autonomous activity will be carried out through the registration of the electrodermal activity (Galvical Skin Reaction), which allows the evaluation the state or emotional reaction of the subjects. The record of electrodermal activity will be measured by the computerized psychophysiological recording equipment I-330-C2 + 12. (J & J Enterprises Seattle, WA). The measuring electrodes will be placed on the distal phalanx of the third and fourth finger of the non-dominant hand with SE-35 sensors connected to a T-601 preamplifier (J & J Enterprises Seattle, WA). For the analysis of results, the USE3 Software from Physiolab will be used (J & J Engineering, 2004).

The analysis of skin conductance data will be carried out with a procedure performed by Benedek and Kaernbach, through which the amplitude of the electrodermal response to a stimulus is obtained. Thus, two register values ​​will be recorded to calculate the amplitude: the conductance recorded in the lowest time of the latency period and the conductance peak. Subsequently, these values ​​and their registration will be subtracted. This analysis will be performed for each event identified in each capsule by each subject, to obtain an average of the conductance amplitudes for each grouping of images-events (positive, negative and neutral).

Between each video there will be a break of 5 to 10 seconds, and before starting the next video for evaluation there will be a neutral sequence in order to calibrate the response of the individual to a neutral state: this is considered to be the washout period between each video.

A parametrization of the measurements will be carried out in order to be able to relate both variables. Subsequently, a survey will be applied to evaluate the recall component.

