***Statistic analysis:***

Hypotheses raised:

- **Study hypothesis 1**

Comparison between capsules and video control

H0: μ capsule X = μ video control

Ha = μ capsule X ≠ μ video control

*μ = average attention, emotional reaction and recall*

- **Study hypothesis 2**

Comparison between groups: men, non-pregnant women, pregnant women

H0: μ1 = μ2 = μ3

Ha: ∃μj ≠ μ j = 1, 2, 3

*μ = average attention, emotional reaction and recall*

- **Study hypothesis 3**

Comparison between levels of schooling: none, primary, baccalaureate, undergraduate, postgraduate

H0: μ1 = μ2 = μ3

Ha: ∃μj ≠ μ j = 1, 2, 3, 4, 5

*μ = average attention, emotional reaction and recall*

- **Study hypothesis 4**

Comparison between family history: children, no children

H0: μ1 = μ2

Ha: μ1 ≠ μ2

*μ = average attention, emotional reaction and recall*

A descriptive analysis of the measured variables will be carried out. The qualitative variables will be described in proportions, and calculations for averages and standard deviation that follow a normal distribution will be performed for quantitative variables. For variables that do not follow this distribution, medians and interquartile ranges will be calculated. The normality of the variables will be evaluated by the Shapiro-Wilk test.

The difference between the averages of the variables of emotional reaction and attention will be carried out by means of an analysis of variance (ANOVA) for dependent samples, taking into account the effect of drag. For these comparisons, the non-parametric tests of Kruskal Wallis and the Wilcoxon rank sum will be used, according to the number of levels of each factor.

For the results of the survey, in which the recall of the contents of the capsules will be evaluated after their screening, an analysis will be made to compare the difference in proportions between the groups with a good level of recall and those with a low level of recall for each category of educational level.

Statistical software Stata 13.1 will be used to analyze the data.

1. **Phase 6. Final production of the health capsules in maternal and neonatal safety**

Professional experts in the layout and development of audiovisual animation products will carry out the final production process, taking into account the changes suggested by the analysis of results of the neuromarketing strategy.

- - - 1. **Ethical considerations**

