The current project adheres to the ethical principles for medical research in human beings, promulgated by the Declaration of Helsinki of the World Medical Association [46] and in the resolution 008430 of 1993 of the Ministry of Health [47], which establishes the scientific, technical and administrative standards for health research. According to this resolution, this investigation is classified as having minimal risk, considering that it uses the data registry through standard procedures and the behavior of the subjects will not be manipulated. For this investigation, a signature of informed consent will be requested for the phases that require it. The entire project will be submitted for approval by an Ethics Committee.

1. **Confidentiality**

The information collected during the development of the project will be restricted to the research team; the information in digital media and databases will have access codes and the information in physical form will be stored on shelves under lock and key for 10 years.

1. **Expected results of the investigation**

After the research is completed, there will be 12 health capsules, designed using neuromarketing strategies, for the preparation of childbirth, both for vaginal delivery and cesarean delivery and the evaluation of their effectiveness in social appropriation of knowledge.

It is hoped that the research, through this strategy of KT, contributes to the knowledge of relevant and clear information for pregnant women and their families and to the empowerment of patients in maternal and neonatal health care. In the medium and long term it is expected that these capsules will be used to be disseminated in a variety of mass media and thus contribute to improve the knowledge and empowerment of the pregnant woman and her family, and in this way the intervention contributes to the improvement of the health and safety of these patients, with a lower proportion of obstetric complications related to pregnancy, childbirth and postpartum.

The project will contribute to the development of the lines of research in maternal and neonatal health and patient safety at the National University of Colombia and the Colombian Society of Anesthesiology and Resuscitation (S.C.A.R.E.).

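### Objective 3 ranks gaze and skin conductance alongside recall as measures of knowledge appropriation, and recall has no described capsule-versus-control test

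*Protocol*

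**What the plan says.** Specific objective 3 (repeated almost unchanged under Aims in the executive summary) evaluates the capsules "in terms of social appropriation of knowledge, measured from attention, emotional response and recall through a pilot study, applying neuromarketing strategies". The opening of Phase 5 lists the same three measures, again without order.

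The Phase 5 process text defines them. For attention, "the eye tracking method will be applied to evaluate the attention of the subjects", with pupil size and fixation recorded. Emotional reaction is electrodermal activity. Recall is a survey given after viewing.

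Hypothesis 1 sets each capsule against the control video on average attention, emotional reaction and recall. The analysis text then reads: "The difference between the averages of the variables of emotional reaction and attention will be carried out by means of an analysis of variance" for dependent samples, with rank-based alternatives for the same comparisons. The survey has its own paragraph, which compares proportions with good and low recall within categories of educational level.

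The sample size section says that its parameters were chosen for recall, with capsules expected to differ moderately from the control video. The expected results promise "the evaluation of their effectiveness in social appropriation of knowledge".

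**The concern.** The stated question is whether the capsules achieve appropriation of knowledge. Two of the three measures offered as evidence record how a viewer looked and how the skin responded. Neither shows that the viewer retained any content. The third measure does bear on content, but the analysis text points it at a different comparison.

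At stake is what a positive result would mean. On the protocol's wording, a capsule that differs from the control video only in gaze or arousal could be reported under the heading of knowledge appropriation. Meanwhile the comparison that would support such a statement is not described.

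**Working it through.** **Does the protocol's framework support the three measures as equals?**

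- Neurocognition and Neuromarketing: activation of attention and emotion, together with a clear and well understood message, is said to predict retention and, to some degree, the effectiveness of a campaign. That makes them predictors of retention, not retention itself.
- The same section describes the electrodermal response as one "which is related to changes in the sympathetic system associated with emotion, cognition and attention". By the protocol's own account, then, it is not specific to emotion, and it is not put forward as a measure of knowledge.
- Current approaches: no existing measure captures knowledge transfer outcomes in this field, so "it is therefore necessary to look for tools to measure changes at the level of knowledge, understanding or attitudes". Recall fits that description. Gaze and skin conductance do not.

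The background therefore separates process measures from the knowledge outcome, and objective 3 merges them.

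**Which outcome was the study sized on?**

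Inputs from the sample size section: one-way fixed-effects ANOVA, f = 0.3, α = 0.05, power 0.90, three groups.

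- Noncentrality λ = f² × N, with degrees of freedom (2, N − 3).
- N = 144: λ = 0.09 × 144 = 12.96, power 0.901. This is the smallest multiple of three that reaches 0.90, so the stated 144 is reproduced.
- N = 150: λ = 0.09 × 150 = 13.5, power 0.913.

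The arithmetic is sound for the test named, and recall is the outcome it was chosen for. That test compares three independent groups, whereas the stated target is capsules against the control video. This is a separate matter and not part of this point.

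**Which comparisons in hypothesis 1 have a described test?**

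Count one average per measure, for 12 capsules against one control video.

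| Measure | Capsule-versus-control comparisons | Test described |
| --- | --- | --- |
| Attention | 12 | ANOVA for dependent samples, or rank-based alternative |
| Emotional reaction | 12 | ANOVA for dependent samples, or rank-based alternative |
| Recall | 12 | None; good versus low recall by educational level |
| Total | 36 | 24 described, 12 not |

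The recall analysis by educational level speaks to hypothesis 3 (schooling), not to hypothesis 1. The executive summary has the same split: dependent-samples ANOVA for emotional reaction and attention, recall by educational level.

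**Is recall required anywhere for an effectiveness conclusion?**

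No. The objective, the hypotheses and the expected results name no leading measure and no rule for combining the three.

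**The case against.** The strongest defence is that recall is not neglected. It is in objective 3, it is in hypothesis 1, it has its own survey, and it drove the sample size. That stands. A reader might infer from objective 3 that a capsule can be declared effective although nobody learned anything. The protocol does not say that. It states no rule that one significant measure is enough, and no rule that all three are needed. Such a rule could sit in an analysis plan that is not shown.

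The process measures also have a declared rationale. The study is a neuromarketing pilot. Attention, emotional commitment and recall are all on the protocol's list of neuromarketing indicators. The background also asks for a range of indicators linked to causal mechanisms. This supports collecting gaze and skin conductance, but not treating them as knowledge outcomes. The knowledge transfer definition, "the synthesis, exchange and application of knowledge by decision makers to accelerate the benefits", concerns decision makers rather than the public, so it carries no weight here.

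Two further inferences fail. One is that a capsule judged effective on physiology alone would go to mass media on that basis. No text makes dissemination depend on such a judgement: 12 capsules are expected in any case, Phase 6 applies changes suggested by the results, and mass-media use with impact evaluation is left to a second stage. The other is that the survey must contain understanding and intention items. The instrument is not in the document, and one of each per capsule would be 12 × 2 = 24 questions. They are optional.

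An unseen analysis plan does not settle the point that remains. The construct is defined in the protocol's objective, and the protocol does describe a recall analysis, aimed at a different comparison from the one in hypothesis 1 and the sample size section.

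**Conclusion.** The concern holds as a mismatch between objective, hypothesis, sizing and analysis. Three unranked measures stand for knowledge appropriation, although the protocol's own background treats two of them as predictors. The one direct knowledge measure, on which 144 (raised to 150) subjects was calculated, has no described capsule-versus-control test: 12 of the 36 comparisons in hypothesis 1. Nothing in the protocol makes recall necessary for an effectiveness conclusion, so the text leaves room for one that rests on physiology alone.

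The count assumes one average per measure per capsule. No error probability is attached, because the protocol states no decision rule from which one could be calculated.

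**What to change.** 1. In objective 3 (and its copy in the executive summary), hypothesis 1 and the expected results, state that effectiveness in knowledge appropriation is concluded from recall, each capsule against the control video, within subject.
2. Add that comparison to the statistical analysis section, with a paired method suited to the form of the recall score, since every participant sees all 13 clips. Keep the analysis by educational level as an additional one.
3. Call attention and electrodermal response supportive process measures. A capsule that differs from the control only on these is reported as more attended or more arousing.

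The cost is wording and one analysis on data already planned, with no change in sample size on this account. One condition needs checking: the analysis text speaks of recall of the capsules' contents, so the survey must also score recall of the control video, clip by clip and on a common scale. If it does not, items for the control have to be added. The downside is that some capsules can no longer be called effective on physiology alone.
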